## **APPROPRIATE PRESCRIBING DEMONSTRATION PROJECT: CLUSTER TRIAL PROTOCOL VERSION 3.0 DATE: 30 May 2016**

### **Background and Rationale**

As part of the 2012 Physicians Services Agreement, the Ministry of Health and Long-Term Care (ministry) and Ontario Medical Association (OMA) established an Appropriate Prescribing Work Group (APWG) tasked to make recommendations to the Physician Services Committee (PSC) on opportunities to improve prescribing in Ontario through voluntary quality-based educational strategies that respect the confidentiality of prescriber practice data. The PSC has approved an initial Demonstration Project of integrated educational strategies starting in Long-Term Care (LTC) homes. The stakeholders decided that appropriate antipsychotic prescribing would be the initial focus of the educational strategies in LTC. This was an appropriate choice as this drug class is known to have substantial risks in the elderly, to be relatively overprescribed given the known risk/benefit ratio, and to be amenable to quality improvement interventions in the LTC setting. The PSC subsequently decided to extend the educational outreach intervention to include falls as a second topic.

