**Primary question:**

What is the effect of adding educational outreach (AF+EO) compared to the ‘usual’ offering of audit and feedback (AF) and communities of practices on:

1. The prescribing of antipsychotic medications in LTC
2. The rate of falls in LTC

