| Depression                                        | Depression rating scale (continuous variable, range 0-14)                             | RAI (DRS_cc)      |
| Falls                                             | Number of falls in the past month (count)                                             | RAI (J4: a)       |
| Secondary health care utilization outcomes |                                                                                       |                   |
| ER visits                                         | Number of ER visits during the previous 6 months (count)                              | CIHI/NACRS        |
| Hospitalizations                                  | Number of hospital visits visit during the previous 6 months (count)                  | CIHI              |

All **primary and secondary prescribing outcomes** will be assessed at baseline (pre-intervention) and at 3 and 6 months post-intervention. Here, "baseline" is defined as the week or month immediately prior to randomization, while post-intervention measurements are defined as the third and sixth months after randomization. These outcomes will be assessed on all residents who are alive at the time of the assessment and who were present in the home for the full duration of the prior week/month.

All **clinical outcomes** (e.g., ADL, behaviour scale, depression, falls) will be assessed at baseline and at 3 and 6 months post-intervention. The most current data collected immediately prior to the implementation of the intervention, and at each post-randomization time point will be used, regardless of mortality status at the subsequent time point.

All **health care utilization outcomes** (number of ER visits and hospitalizations during the previous 6 months) will be assessed at baseline and at 6 months post-intervention. A longer duration is required to allow adequate time for the intervention to have an effect on these outcomes. All residents present in the homes at any time during the study will contribute to the analysis using person-time of follow-up. As the EO intervention may be rolled out over a 2-3 month period due to logistical restraints, homes allocated to the control arm will have their measurement times assigned randomly from the assessment times of the intervention homes in the same stratum.

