**Secondary clinical outcomes** measured as continuous variables (e.g., ADL, depression score) will be analyzed using linear mixed effects regression with normal distribution and identity link. Fixed and random effects will be specified as described for the prescribing outcomes. The effect of the intervention will be expressed as adjusted least square mean differences with 95% CI. Secondary clinical outcomes measured on an ordinal scale (e.g., pain scale) at baseline, 3 months and 6 months will be analyzed using generalized mixed effects regression as described for the primary outcome but using multinomial distribution and cumulative logit link. Presence of any falls in the past 30 days will be analyzed at baseline, 3 months, and 6 months using generalized linear mixed effects regression with binomial distribution and logit link, as described for the primary outcome. In the Intent-To-Treat analyses for the secondary clinical outcomes (e.g., ADL, falls, pain), the potential effect on inferences of patients who died will be examined using sensitivity analyses under conservative assumptions: for example, patients who died during the interval will be assigned the worst possible score. Depending on the extent of patient turnover within homes, additional analyses for primary and secondary outcomes will explore inclusion of subject-specific random effects to account for repeated measures on the same patient over time (i.e., a cohort rather than cross-sectional design).

**Health care utilization outcomes** (number of ER visits and hospital visits) will be analyzed at 6 months using generalized linear mixed-effects regression with Poisson or negative binomial distribution and log-link, with log person-time of follow-up as an offset term. The following fixed effects will be included: intervention, phase, and stratification variables, as well as the rate of health care utilization at the home 6 months prior to the intervention. Patient covariates will be adjusted for as specified for the primary outcome. Home will be included as a random effect. The effect of the intervention will be expressed as adjusted Rate Ratio (RR) with 95% CI.

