| 20 homes
PHASE 1             |                                 | Allocated to
EO (Topic 1) |                                 | Qualitative
process
evaluation | 6M follow
up
complete     |                                 | 6M ICES
ODB data
complete |                          |                                      |                                 |                                                           |
| 20 + homes
PHASE 1           |                                 | Allocated to
AF only      |                                 | Qualitative
process
evaluation | 6M follow
up
complete     |                                 | 6M ICES
ODB data
complete |                          |                                      |                                 | Potential
launch of
EO (if
scale-up
approved) |
| 20 homes
PHASE 2             |                                 |                              |                                 |                                      | Allocated
to EO
(Topic 1) |                                 |                                 | 6M follow
up complete |                                      | 6M ICES
ODB data
complete |                                                           |
| Topic 2 (Falls)                 |                                 |                              |                                 |                                      |                                 |                                 |                                 |                          |                                      |                                 |                                                           |
| All
Intervention
Homes
(n=40) |                                 |                              |                                 |                                      |                                 | Introduction of
EO Topic 2   |                                 |                          | Qualitative
process
evaluation |                                 |                                                           |

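### Falls is part of the primary question, but its 3- and 6-month assessments run from randomisation, so about half the outreach homes finish follow-up before falls outreach starts and the falls contrast is diluted and mixed

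*Protocol*

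**What the plan says.** **Status of falls.** Background and Rationale says: "The PSC subsequently decided to extend the educational outreach intervention to include falls as a second topic". The Primary question section lists, as its second item, "The rate of falls in LTC". Elsewhere falls is secondary. Secondary question ii names it as an example of an outcome linked to antipsychotics, the outcome table places it under secondary clinical outcomes, and the Analysis section handles it in the paragraph on those outcomes. The only primary outcome in the table is antipsychotic dispensing, and the Power section does not cover falls.

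**Timing.** Outcomes says of the clinical outcomes: "e.g., ADL, behaviour scale, depression, falls) will be assessed at baseline and at 3 and 6 months post-intervention". The paragraph before it, on prescribing outcomes, explains that "post-intervention measurements are defined as the third and sixth months after randomization". The clinical paragraph has no such definition, but it too describes its follow-up points as counted from randomisation. Analysis repeats the schedule: "Presence of any falls in the past 30 days will be analyzed at baseline, 3 months, and 6 months".

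**Calendar.** In the Implementation timeline, 20 Phase 1 homes are allocated to Topic 1 outreach in September-October 2015, with "6M follow up complete" in March-April 2016. Twenty Phase 2 homes are allocated in March-April 2016 and complete 6 months in September-October 2016. The Topic 2 row, for all 40 intervention homes, shows "Introduction of EO Topic 2" in May-June 2016 and a qualitative process evaluation in November-December 2016. It shows no quantitative follow-up.

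**Form of the endpoint.** The primary question asks about a rate, the outcome table gives "Number of falls in the past month (count", and the Analysis section models the presence of any fall.

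**The concern.** The protocol adds a second outreach topic aimed at falls and puts falls in the primary question, but keeps the measurement schedule built for the first topic. If the 3- and 6-month points run from randomisation, some homes counted as receiving outreach are assessed before any falls outreach exists. In those homes the contrast can show only what antipsychotic outreach does to falls. Pooled with the later homes, it understates any effect of outreach that includes the falls topic. The project is meant to inform a scale-up decision, so a null falls result could be taken as evidence that falls outreach does not work.

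**Working it through.** **1. Calendar check.** Count months from 1 September 2015 as month 0, using the two-month columns of the timeline.

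| Event | Column | Months |
|---|---|---|
| Phase 1 allocated | Sept-Oct 2015 | 0-2 |
| Phase 1, 6 months later | Mar-Apr 2016 | 6-8 |
| Phase 2 allocated | Mar-Apr 2016 | 6-8 |
| Topic 2 introduced | May-June 2016 | 8-10 |
| Phase 2, 3 months later | June-Aug 2016 | 9-11 |
| Phase 2, 6 months later | Sept-Oct 2016 | 12-14 |

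Both 6-month completion columns reproduce: 0-2 plus 6 gives 6-8, and 6-8 plus 6 gives 12-14.

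**2. Exposure to falls outreach at assessment.**
- Phase 1: follow-up closes in months 6-8 and Topic 2 starts in months 8-10. Exposure is nil at both 3 and 6 months.
- Phase 2 at 6 months: least 12 − 10 = 2, most 14 − 8 = 6, midpoint 13 − 9 = 4 months.
- Phase 2 at 3 months: midpoint 10 − 9 = 1 month.
- The table text was extracted from a PDF. If the Topic 2 cell belongs to July-August (months 10-12), Phase 2 exposure at 6 months is 0 to 4 months with midpoint 2, and at 3 months the midpoint is 10 − 11 = −1, that is, none. Phase 1 is unchanged.

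**3. Share of homes.** On the timeline, 20/40 = 50%. The Allocation and Power sections cap outreach at 38 homes, and 20/38 = 53%, still about half.

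**4. Does the planned model separate the two groups?** Analysis includes phase as a fixed effect. A phase main effect lets the outcome level differ between phases. It does not let the intervention effect differ, so one effect is still averaged over unexposed and partly exposed homes. Control homes take their measurement times at random from intervention homes in the same stratum, so they inherit the same Topic 1 schedule.

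**5. Illustration of dilution.** The protocol gives no ICC, target effect or power for falls, so there is no figure of its own to reproduce.

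Inputs from the protocol: 30-day falls prevalence in Ontario 14.8% (falls background); 30 and 15 clusters and 120 residents per home (Power); 5% significance level (Analysis). Assumptions: true odds ratio 0.70 in exposed homes; half the outreach clusters unexposed and half fully exposed; no effect of Topic 1 on falls; ICC 0.01 (the protocol's value for its ordinal outcome), 0.02 (assumed) and 0.1 (its value for a dichotomous outcome).

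- Control odds: 0.148/0.852 = 0.1737.
- Exposed homes: 0.70 × 0.1737 = 0.1216, risk 0.1216/1.1216 = 10.8%.
- Outreach arm average: (10.84% + 14.8%)/2 = 12.8%.
- Apparent odds ratio: (0.1282/0.8718)/0.1737 = 0.85.

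Power is Φ(|log OR|/SE − 1.96), with SE² = 1/[n₁p₁(1−p₁)] + 1/[n₀p₀(1−p₀)], n₁ = 3600/DE, n₀ = 1800/DE and DE = 1 + 119 × ICC.

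| ICC | DE | All homes exposed (OR 0.70) | Half exposed (OR 0.85) |
|---|---|---|---|
| 0.01 | 2.19 | 0.357/0.126 = 2.83, power 81% | 0.167/0.123 = 1.36, power 27% |
| 0.02 | 3.38 | 0.357/0.157 = 2.27, power 62% | 0.167/0.153 = 1.09, power 19% |
| 0.1 | 12.90 | 0.357/0.306 = 1.16, power 21% | 0.167/0.298 = 0.56, power 8% |

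A difference-in-proportions calculation agrees closely: 80% to 28% at ICC 0.01, and 22% to 9% at 0.1.

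**The case against.** The strongest reply is that the protocol mostly treats falls as secondary. For secondary question ii, where falls is a possible harm of antipsychotics, a 3- and 6-month clock from randomisation is coherent. That stands. The timing problem bites because the Primary question section also lists falls, and the two positions have to be reconciled.

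Second, a reader might infer that the falls question cannot be answered at all. The documents do not support that. The question asks about adding educational outreach, not falls outreach alone, and an intention-to-treat contrast of the randomised arms can be computed. Topic 1 might also affect falls, since the background links antipsychotics to falls. The contrast is diluted and mixed, not impossible.

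Third, the clock is not fixed beyond doubt. The explicit definition sits in the prescribing paragraph, and the clinical paragraph ties baseline to implementation of the intervention. But that paragraph also counts follow-up from randomisation, and no Topic 2 schedule appears anywhere. The randomisation reading is the natural one.

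Fourth, a reader might take the fall from 81% to 27% as the trial's actual loss of power. It is not. It depends on a low ICC and an assumed effect; at the protocol's dichotomous ICC of 0.1, power would be low even without dilution. Treating Phase 2 homes as fully exposed understates the dilution, while ignoring any Topic 1 effect may overstate it.

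**Conclusion.** The concern holds as a timing and status inconsistency. Followed as written, the plan gives a falls estimate in which about half the outreach homes (20 of 40 shown) had no falls outreach at either assessment, and the rest had about 2 to 6 months of it at the last one. This rests only on the timeline and the randomisation clock, and every plausible reading of the Topic 2 column leaves the Phase 1 result the same. The size of the dilution is illustrative: an odds ratio of 0.70 appearing as about 0.85 requires the stated assumptions on prevalence, exposure and Topic 1 effect, and the power figures also require an assumed ICC. A null falls result on this schedule would not show that falls outreach is ineffective. The three forms of the endpoint (rate, count, yes/no) are a smaller inconsistency to settle in the same revision.

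**What to change.** Reconcile the Primary question, secondary question ii, the outcome table, the Analysis section and the timeline.

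**If falls stays primary:**
- Anchor its follow-up at 3 and 6 months after the Topic 2 introduction (about August-September and November-December 2016), with the same calendar windows for all randomised intervention and control homes.
- Keep the pre-randomisation assessment as baseline, so that the randomised comparison of outreach plus audit and feedback with audit and feedback alone is preserved. A baseline just before Topic 2 falls after randomisation and after Topic 1 allocation, so it would subtract any Topic 1 effect on falls. It could serve as a supplementary analysis with that caveat.
- Use one falls definition in the question, outcome table and model.
- Report falls on the Topic 1 clock as the secondary outcome for question ii.
- Apply the Topic 2 windows to any fall-risk drug outcomes used for question iv.

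**Otherwise:** state that falls is secondary and that the result on the Topic 1 clock does not estimate the effect of falls outreach.

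**Cost:** wording and an extra extraction of administrative data. The falls result comes later, by an amount that depends on the annual CCRS release described in the Analysis section. The timeline shows control homes with no outreach before March 2017, so both windows fit. The protocol is dated 30 May 2016, around the planned Topic 2 start.

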### **Analysis**

Descriptive statistics will be calculated for all variables of interest: continuous variables with a normal distribution will be described using means and standard deviations (medians and inter-quartile ranges in the case of skewed distributions), whereas categorical variables will be summarized using frequencies and proportions. All analyses will be by Intention To Treat. Analyses will be conducted using SAS v.9.3 and statistical significance will be assessed at the 5% level.

The **primary outcome** describing **dispensing of medication** (number of days with antipsychotic/benzodiazepine/antihypertensive/anticholinergic prescriptions in the last week) will be analyzed using generalized linear mixed effects regression with multinomial distribution and cumulative logit link. To account for the staggered implementation of the intervention, phase (phase1/phase2) will be included as a fixed effect. Random intercepts and slopes will be specified to account for intracluster

and inter-period correlations. To maximize statistical efficiency, the analysis of prescribing outcomes will adjust for the stratification factors as well as public/private home ownership and the following patient covariates: age, sex, levels of function and aggressive behaviour (using multiple imputation for missing covariates if necessary). The effect of the intervention at 6 months will be expressed as cumulative Odds Ratio (OR) with 95% confidence interval (CI). In case of non-convergence or violation of the proportional odds assumption using the score test, the normal distribution and identity link will be used. The dichotomous **prescribing** outcomes (i.e., any relevant prescription in the last month) at baseline, 3 months, and 6 months will be analyzed using generalized linear mixed effects regression with binomial distribution and logit link function. Fixed and random effects will be specified as described for the primary outcome. The fixed effects of time, intervention, and intervention by time will be the main variables of interest. Dose equivalent of antipsychotic dispensed in the past month at baseline, 3 months, and 6 months will be analyzed using linear mixed effects regression with normal distribution and identity link. Fixed and random effects will be specified as described for the primary outcome. The effect of the intervention will be described as difference in change from baseline to 6 months using adjusted least square means with 95% CI. In the case of substantial skewness, gamma distribution with log link or log-normal distribution will be considered, and difference in change from baseline will be expressed as adjusted relative mean difference with 95% CI.

**Secondary clinical outcomes** measured as continuous variables (e.g., ADL, depression score) will be analyzed using linear mixed effects regression with normal distribution and identity link. Fixed and random effects will be specified as described for the prescribing outcomes. The effect of the intervention will be expressed as adjusted least square mean differences with 95% CI. Secondary clinical outcomes measured on an ordinal scale (e.g., pain scale) at baseline, 3 months and 6 months will be analyzed using generalized mixed effects regression as described for the primary outcome but using multinomial distribution and cumulative logit link. Presence of any falls in the past 30 days will be analyzed at baseline, 3 months, and 6 months using generalized linear mixed effects regression with binomial distribution and logit link, as described for the primary outcome. In the Intent-To-Treat analyses for the secondary clinical outcomes (e.g., ADL, falls, pain), the potential effect on inferences of patients who died will be examined using sensitivity analyses under conservative assumptions: for example, patients who died during the interval will be assigned the worst possible score. Depending on the extent of patient turnover within homes, additional analyses for primary and secondary outcomes will explore inclusion of subject-specific random effects to account for repeated measures on the same patient over time (i.e., a cohort rather than cross-sectional design).

**Health care utilization outcomes** (number of ER visits and hospital visits) will be analyzed at 6 months using generalized linear mixed-effects regression with Poisson or negative binomial distribution and log-link, with log person-time of follow-up as an offset term. The following fixed effects will be included: intervention, phase, and stratification variables, as well as the rate of health care utilization at the home 6 months prior to the intervention. Patient covariates will be adjusted for as specified for the primary outcome. Home will be included as a random effect. The effect of the intervention will be expressed as adjusted Rate Ratio (RR) with 95% CI.

Potential effect modification by ownership status of LTC home and staffing ratios, size of the home (<65 beds, 65-129 beds, or >129 beds), location (urban/rural), specialist utilization (proportion of patients with geriatrician or psychiatrist consultation within 6 months), plus primary physician characteristics (sex, years' experience), as well as patient characteristics (age, sex, time at facility, levels of function and aggressive behaviour plus whether a geriatrician or psychiatrist provided a consult) will be explored by including interactions between these variables and: time, treatment, and treatment by time.

Although primary analyses will examine outcomes for all patients excluding those with known to be palliative or with a history of bipolar disorder, schizophrenia or Huntington's disease, planned sub-group analyses will focus on those with dementia. A planned sensitivity analysis will restrict the educational

outreach cohort to physicians who also accessed the audit and feedback to examine for synergy in the full intervention group. We do not anticipate substantial missingness on prescribing or health care utilization outcome; however, exploratory analyses will be carried out to identify the extent of missing data on resident clinical and demographic variables (e.g., levels of function, aggressive behaviour, depression). If more than 5% of residents have missing data at any time, we will create a complete data set for analysis using multiple imputation, where the imputation model will include all covariates of interest in subsequent primary and secondary outcome analyses, as well as those variables identified as associated with missingness.

Since the CCRS data is only released for linkage at ICES annually, a planned interim analysis will compare the primary and secondary prescribing outcomes (which use ODB data). No stopping rules are planned based on this interim analysis; the results will be considered tentative and used only for confidential reporting to the funders.

Qualitative data will be analyzed using Charmaz's textual analysis method (Charmaz, 2014). NPT and the CFIR, used to inform the development of the interview guides, will be used to guide coding and analysis of the qualitative data (Damsroder et al., 2009; MacFarlane et al., 2012). In the final analytical phase, the investigative team and research personnel including trainees will prepare a comprehensive case study database with the datasets from each of the research questions (Yin, 2009). Enhancing credibility of case study design involves the use of multiple data sources and methods (Yin, 2009). We will triangulate key themes, categories and codes comparing and contrasting the case study database with the evolving programme theory hypotheses (cross-syntheses). Through a series of 2-3 analytical sessions, the case report will be finalized. We will employ a variety of strategies to ensure fidelity and credibility of the data: 1) using multiple sources of data, writing a chain of evidence that describes all elements of the case study database and a description of the derivation of the evidence from initial research questions to ultimate case study conclusions, and having key informants review the case study draft by having collaborators participate in the triangulation analysis and the return of findings (construct and external validity); 2) examining points of convergence (pattern matching) and divergence (examining alternative explanations) within and amongst the various datasets (internal validity through cross comparative analyses); and 3) creating a case study database with a chain of evidence, and having a stepped analysis process whereby there is an initial independent review of the data (transcripts, field notes) by at least 3 reviewers who then meet to reach consensus around the common themes (reliability) (Kidder and Judd, 1986; Lincoln and Guba, 1985).

We will analyse process evaluation data from clinician surveys after the intervention has been completed. Baseline data evaluation will include descriptive statistics, psychometric properties, and exploration of the association between process variables as a preliminary test of the theorised process models. This will be conducted by a statistician without knowledge of group allocation. Measures of capability, opportunity, and motivation will be calculated as the mean of the measure item scores.

We will use analytical methods previously developed to test for differences between groups on hypothesised targeted constructs, controlling for baseline differences (Grimshaw et al., 2007).

Mediation models will be used to test whether intervention effects on behaviour are mediated through the targeted theoretical constructs.

